## Abstract

**Background:**

There is an ongoing discussion about the advantages and disadvantages of different surgical positions (semi-sitting and lateral position) for vestibular schwannoma surgery. Each position has its advantages, disadvantages, challenges, and risk profiles. The objectives of this study are to compare the effects of different surgical positions (semi-sitting and lateral position) on the outcomes of large vestibular schwannoma, primarily including effectiveness and safety.

**Methods:**

In this single-centre, open, randomized controlled trial, we will recruit a total of 116 participants according to the inclusion and exclusion criteria who will be randomized to an experimental group or control group. Patients will undergo operations in semi-sitting and lateral positions. The primary endpoint will be the percentage of gross total resection. The secondary endpoints will include the facial nerve function, hearing preservation, surgical position placement time, time of operation (skin-to-skin surgical time), hospital stay, total hospitalization fee, and complications. The follow-up period will be at least 12 months, during which time patients will be evaluated both clinically and radiologically.

**Discussion:**

This issue is still debated after 30 years since the first large comparative study was published in 1989, so the study will be useful. Therefore, more high-quality studies are required to compare clinical outcomes, complications, and other factors associated with these two positions.

**Trial registration:**

Chinese Clinical Trial Registry ChiCTR1900027550. Registered on 17 November 2019

## Introduction

### Background and rationale {6a}

Vestibular schwannoma (VS) is a common intracranial space-occupying lesion, accounting for approximately 6–10% of intracranial tumours. VS most often develops from the vestibular nerve of the internal auditory canal segment. Its origin is the Schwann cell cover of the eighth cranial nerve. Early auditory disorders, such as hearing deterioration and tinnitus, are common first symptoms [1–5]. However, space exists in the cerebellopontine area (CPA), and some patients have large tumours without any symptoms. Although VS exhibits a benign pathologically, tumours can eventually become life-threatening as brainstem compression increases. Regarding treatment, controversy still exists, but the current strategy depends substantially on the tumour size. Generally, for small tumours, conservative management or radiosurgery can be used, whereas surgery is inevitable in large or growing tumours [5–9]. However, some scholars have noted that tumour removal should be performed at the earliest stage as much as possible, especially for large tumours (Koos 4) accompanied by obvious brainstem and cerebellum compression [10–12].

The goals of modern VS surgery are to completely remove the tumour, preserve nerve function, and reduce complications. In recent years, with the popularization and application of microscopy, continuous improvements in surgical instruments and skills, in-depth studies of the microanatomy of the cerebellopontine angle, and the application of intraoperative electrophysiological monitoring technology, the above surgical goals have largely been attained [12–15]. In addition, many factors affect the outcomes of surgery and related complications, among which the effect of different surgical positions has long been debated. Patients are easily placed in the lateral position (LP, Fig. 1B), and few complications are associated with this surgical position. However, corresponding disadvantages do exist, such as high cranial pressure, difficulty in releasing cerebrospinal fluid, unclear anatomical location, and increased requirements for assistants [5]. In contrast, the semi-sitting position (SSP, Fig. 1A) provides specific possible advantages, including drainage of blood and cerebrospinal fluid (CSF) by gravity, decreased bleeding, clean surgical field, improved surgical exposure and anatomical orientation, and ability to perform continuous bimanual dissection [5, 15–18]. However, this position carries some potential risks, such as venous air embolism (VAE) [19], tension pneumocephalus, and peripheral nerve injury [16, 20]. Despite these risks, some neurosurgeons preferred to perform posterior fossa surgeries in the SSP [15, 21]. Many studies have shown that the operational risk associated with body position is very low in the context of adequate preoperative preparation, intraoperative coordination with anaesthesiologists, and careful monitoring. Thus, SSP is safe and reliable [22–24]. [name] of Hannover, Germany, personally completed more than 4000 cases of semi-sitting VS resection. Long-term functional outcomes and surgery-related complication rates were satisfactory. Fifty patients with VSs > 4.0 cm in maximal extra-meatal diameter were reported with gross total resection, and the anatomical integrity of the facial nerve was preserved in 92% [25]. Taking all the above-mentioned advantages into consideration, SSP may lead to better surgical outcomes, such as a higher percentage of gross total resection and better facial nerve function, for patients with large VSs. However, randomized studies are required to verify this hypothesis.

**Fig. 1 Fig1:**
[figure not shown]
Semi-sitting position (**A**) and lateral position (**B**)

Literature searches were performed in August 2019 and then updated in February 2020 using the PubMed database. We identified a few studies that reported the surgical results of SSP compared with LP on the VS, including a randomized, multicentre trial and a few retrospective studies. These results and conclusions of different studies are quite different, and the evaluation indexes in various studies are relatively limited. Further comprehensive and in-depth research is needed. We also conducted a comprehensive search on the ClinicalTrials.gov and Chinese Clinical Trial Registry and found no similar prospective randomized controlled trials (RCTs) that are ongoing or completed.

### Objectives {7}

The objectives of this study are to compare the effects of different surgical positions (SSP and LP) on the outcomes of large VS, primarily including effectiveness and safety.

### Trial design {8}

This trial will be designed as a single-centre, open, RCT to assess the effects of different surgical positions (SSP and LP) on the surgical outcomes of large VS. The protocol was reported using the recommendations of Standard Protocol Items: Recommendations for Interventional Trials (SPIRIT) [26]. The open mode is the only possible choice for this trial because it is impossible to hide the surgical position of each patient. However, to minimize bias related to the “open” mode, the evaluation of some outcomes and the statistical analysis will be performed in a blinded fashion. The schedule of enrolment, interventions, and assessments for all study patients can be found in Fig. 3.

### Eligibility criteria {10}

Participant recruitment will be performed at our tertiary referral neurotological centre. Patients with VSs who fulfil the inclusion criteria and sign the informed consent forms will enter the screening period. Participants who meet the exclusion criteria will be excluded before randomization. Figure 2 shows the flow chart of the study. In this trial, patients who met the inclusion and exclusion criteria will be randomly assigned to two parallel groups, namely, an experimental group or a control group, and the baseline data of each patient will be collected carefully. The details of the inclusion and exclusion criteria and withdrawal criteria are provided in Table 2.

**Fig. 2 Fig2:**
[figure not shown]
Flow diagram of this single-centre, open, randomized controlled trial

**Table 2 Tab2:** Inclusion and exclusion criteria and withdrawal criteria

**Inclusion criteria**	
Age between 18 and 65 years old, regardless of gender	
Preoperative imaging diagnosis of VS, Koos grade 4	
Preoperative American Society of Anaesthesiologists (ASA) score 1–2 [27, 28]	
Preoperative evaluation of facial nerve function for House-Brackmann (HB) grading system I level [29]	
**Exclusion criteria**	
History of any forms of therapies, such as radiotherapy and operation	
Cervical spondylolisthesis and cervical instability	
Diagnosis of neurofibromatosis type 2 (NF2)	
**Withdrawal criteria**	
Patient wishing to interrupt participation in the study before the end	
Patient has a patent foramen ovale^a,b^	
Postoperative pathological diagnosis is non-schwannoma	

*VS* Vestibular schwannoma

^a^Screening method for the preoperative detection of a patent foramen ovale (PFO) for patients with planned SSP is transoesophageal echocardiography (TEE)

^b^If the patient has a PFO, he or she will not be excluded from the study, but the surgical position originally assigned will be changed to LP

### Additional consent provisions for collection and use of participant data and biological specimens {26b}

Not applicable as no biological specimens were collected as part of this trial.

### Interventions

#### Explanation for the choice of comparators {6b}

The details are provided in Table 3.

**Table 3 Tab3:** Primary and secondary outcomes

**Primary outcome**		
Percentage of gross-total resection		
Extent of tumour resection	Gross total resection: total resection under the microscope, imaging without residual.	Note: The evaluation of total resection under the microscope and determination of microscopic residual tumours depend largely on subjective observations from experienced neurosurgeons according to the operation video.
	Near-total resection: microscopic residual (a few tumour capsules, < 5%), imaging no residual.	
	Subtotal resection: microscopic residual (small tumour remnant, 5–10%), imaging small tumour remnant residual.	
	Partial resection: microscopic nodular residual tumour (≥ 10%), imaging nodular residual tumour.	
**Secondary outcomes**		
Facial nerve function	As one of the inclusion criteria, facial nerve function was documented photographically at rest and while performing standardized facial expressions at defined time points (preoperatively, discharge, and 6 and 12 months after surgery).	This feature was evaluated by two experienced neurologists and classified according to the HB grading system [29].
Hearing function	Hearing level will be analysed and evaluated using pure-tone audiometry (PTA) and speech discrimination score (SDS) according to the guidelines of the American Association of Otolaryngology–Head and Neck Surgery (AAO-HNS) classification [30].	Serviceable hearing was defined as either class A (PTA ≤ 30 dB, SDS ≥ 70%) or class B (30 < PTA ≤ 50 dB, SDS ≥ 50%) and non-serviceable hearing as class C (PTA > 50 dB, SDS ≥ 50%) or class D (any PTA, SDS < 50%).
Surgical positioning time		
Time of operation	Craniotomy time	
	Intradural microsurgery time	
	Scalp closure surgery time	
Hospital stay		
Total hospitalization fee		
General complications	Intracranial haematoma: head imaging examination will be performed within 3 h after surgery.	
	Cerebrospinal fluid leakage (incision leakage or nasal leakage).	
	Intracranial infection: postoperative fever, cerebrospinal fluid routine, and biochemical evidence of infection.	
	Cranial nerve disorders in the posterior group: drinking water choking cough, articulation disorder, etc.	
	Others	
Special complications	VAE	
	Others	
Recurrence		

*HB* House-Brackmann, *VAE* Venous air embolism

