#### Plans to promote participant retention and complete follow-up {18b}

The follow-up period will be at least 1 year, during which time the patients will be evaluated both clinically and radiologically. After surgery, all patients will be regularly examined at the outpatient clinic every 3–6 months. Clinical assessments, such as facial nerve function (according to the HB grading system) and hearing function (according to the AAO-HNS classification), will be performed. Postoperative MRI will be performed before discharge and 3 months after surgery. Further follow-up examinations will be performed every year. No interim analyses are planned.

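### The hearing classes printed in Table 3 leave out patients with PTA of 30 dB or better and SDS of 50–69%, who are then neither serviceable nor non-serviceable

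*Protocol article*

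**What the plan says.** Hearing preservation is one of the secondary endpoints listed in the protocol article under Outcomes {12}. The detail is in Table 3, in the row on hearing function. Hearing is to be assessed by PTA and SDS, "according to the guidelines of the American Association of Otolaryngology–Head and Neck Surgery (AAO-HNS) classification [30" being the reference cited there. The same row then gives its own numeric cut-offs:

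- Class A: "Serviceable hearing was defined as either class A", with PTA at most 30 dB and SDS at least 70%.
- Class B, also serviceable: "class B (30 < PTA ≤ 50 dB, SDS ≥ 50" percent.
- Class C: "non-serviceable hearing as class C (PTA > 50 dB, SDS ≥ 50" percent.
- Class D, also non-serviceable: "class D (any PTA, SDS < 50" percent.

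Hearing level is among the baseline data to be collected (sections {18a} and {19}). At follow-up, section {18b} says only that "hearing function (according to the AAO-HNS classification), will be performed", without cut-offs. Section {20a} compares hearing function between the two positions by Fisher's exact or chi-squared test. It also makes hearing function an outcome of a regression on position, tumour size, surgeon and extent of resection. None of these places says what to do with a PTA and SDS pair that fits no class.

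**The concern.** A classification that feeds a categorical test should give every patient exactly one category. Class A requires SDS of at least 70%, whereas class B accepts SDS down to 50% but only when PTA is above 30 dB. A patient with good tone thresholds and a moderately reduced speech score therefore seems to miss both. Such a patient also misses C, because PTA is not above 50 dB, and D, because SDS is not below 50%.

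The result also runs the wrong way. With the speech score held fixed, a patient whose tone thresholds improve from 35 dB to 25 dB moves from serviceable to unclassified.

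What is at stake is a named secondary endpoint. Both analyses in {20a} need a category for each patient. Section {17a} gives outcome evaluation to a third party not involved in the study, and that party needs a complete written rule.

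**Working it through.** **Inputs.** These are the four class definitions exactly as printed in Table 3. The plan states no figure to reproduce, so the check is of the logic of the rule.

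**Step 1: one case by hand.** Take PTA 25 dB and SDS 60%.

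| Class | PTA condition | SDS condition | PTA 25, SDS 60 | PTA 35, SDS 60 |
|---|---|---|---|---|
| A | ≤ 30 | ≥ 70 | fails (SDS) | fails (both) |
| B | > 30 and ≤ 50 | ≥ 50 | fails (PTA) | **meets** |
| C | > 50 | ≥ 50 | fails (PTA) | fails (PTA) |
| D | any | < 50 | fails (SDS) | fails (SDS) |

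The patient with better thresholds has no class. The patient with worse thresholds and the same speech score is class B.

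**Step 2: all combinations.** The rules were applied to every whole-number pair with PTA from 0 to 120 dB and SDS from 0 to 100%, which is 121 × 101 = 12,221 pairs.

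- Class A: 31 PTA values × 31 SDS values = 961
- Class B: 20 × 51 = 1,020
- Class C: 70 × 51 = 3,570
- Class D: 121 × 50 = 6,050
- Sum: 961 + 1,020 + 3,570 + 6,050 = 11,601
- Without a class: 12,221 − 11,601 = 620

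No pair met more than one class. The 620 pairs are exactly PTA 0–30 dB (31 values) with SDS 50–69% (20 values), and 31 × 20 = 620. On a continuous scale the gap is PTA ≤ 30 dB with 50% ≤ SDS < 70%. These counts show where the gap lies. They say nothing about how many patients fall in it, because patients are not spread evenly over the grid.

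**Step 3: what the printed non-serviceable definition implies.** Classes C and D together are PTA > 50 dB or SDS < 50%. The complement is PTA ≤ 50 dB with SDS ≥ 50%. As printed, classes A and B cover that complement except for the cell found in step 2.

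**Step 4: the rule without the lower bound.** Let class B be PTA ≤ 50 dB and SDS ≥ 50%, not meeting class A. On the grid this gives 51 × 51 − 961 = 1,640 pairs, which is 1,020 + 620. The total becomes 961 + 1,640 + 3,570 + 6,050 = 12,221. Every pair now has exactly one class, and no pair that already had a class has changed.

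**Step 5: size.** The document gives no distribution of PTA or SDS, so the number of patients in the gap cannot be estimated. As a scale only: with all 58 patients of an arm in the denominator, one patient moved between categories shifts that arm's proportion by 1/58 = 1.7 percentage points.

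**The case against.** The strongest reply is that the governing rule is the cited AAO-HNS classification. Table 3 invokes it and section {18b} repeats it, so the bracketed cut-offs may be only a short summary in a table cell of a journal article. This stands in part. A reader might infer that hearing status cannot be determined at all for these patients, and the document does not support that, since the cited classification may place them. It is not at hand, so this cannot be checked. The reply does not rescue the printed text, however. The article chose to give numeric bounds, and those bounds fail. If the guideline covers the cell, the printed rule departs from its own reference; if it does not, the gap is real in both.

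Two further inferences should be resisted.

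- *Affected patients would be dropped or counted as non-serviceable.* The document says neither. Non-serviceable is defined as class C or D, and these patients are in neither class.
- *The loss is magnified because preservation is judged only among patients with serviceable hearing at baseline.* The article names hearing preservation but states no such restriction, and {20a} compares hearing function between arms without one.

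It is also fair to say that the same rule applies to both arms and that section {17a} has outcomes evaluated blind to allocation. No direction of bias follows.

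**Conclusion.** The definition printed in Table 3 is incomplete. Patients with PTA at or below 30 dB and SDS from 50% to under 70% have no class, and this follows from the lower PTA bound on class B alone. It is an error in a stated rule, not a detail left to another document, and no other section of the article closes it. Applied as printed, the hearing category of such patients is undefined at baseline and at follow-up, and the comparison in {20a} would depend on how someone chose to handle them.

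The importance is limited. Hearing is one of several secondary outcomes, and the primary endpoint and the sample size are untouched. The number of patients affected is unknown, may be small and could be zero. The logical finding rests on the printed bounds only. The one open point is whether the cited classification already places these patients.

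**What to change.** In Table 3, define class B as PTA at most 50 dB and SDS at least 50%, not meeting class A. Serviceable hearing is then PTA at most 50 dB with SDS at least 50%, the exact complement of classes C and D as they stand. Every combination gets one class, and no patient who already has a class is moved. Before hearing data are analysed, the authors should check this wording against the cited classification and state the agreed rule in full for the outcome evaluators. The cost is one phrase in Table 3, with no new data and no extra visits.

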#### Intervention description {11a}

All surgeries will be performed via the retrosigmoid approach with intraoperative neurophysiological monitoring (brainstem auditory evoked potentials, continuous facial nerve electromyography, and direct facial nerve stimulation). All surgeries will be performed by two experienced neurosurgeons ([name] and [name]). Both surgeons will operate on patients in the SSP and LP. Before this clinical trial, they performed at least 200 VS surgeries with SSP and LP, respectively. They have no preference regarding the SSP and LP and are skilled in operating under both positions. Both surgeons will operate on patients in the SSP and LP. The LP adopted by the control group is a conventional position for neurosurgery, while the SSP is adopted by the experimental group, which is similar to that reported in the Frankfurt Protocol [23].

#### Criteria for discontinuing or modifying allocated interventions {11b}

The details are provided in Table 1.

#### Strategies to improve adherence to interventions {11c}

Not applicable as the interventions are all surgery.

#### Relevant concomitant care permitted or prohibited during the trial {11d}

Relevant concomitant care, such as hypertension and diabetes, is permitted during the trial.

#### Provisions for post-trial care {30}

Even after the clinical trial is finished, a long-term follow-up will be achieved in each patient.

### Outcomes {12}

The primary endpoint will be the percentage of gross total resection. The secondary endpoints will include facial nerve function, hearing preservation, surgical position placement time, time of operation (skin-to-skin surgical time), hospital stay, total hospitalization fee, and complications. The details of the primary and secondary outcomes are provided in Table 3.

#### Participant timeline {13}

The timeline is shown in Fig. 3.

**Fig. 3 Fig3:**
[figure not shown]
Schedule of enrolment, interventions, and assessments for all study patients

#### Sample size {14}

The sample size was calculated from the primary endpoint. We calculated the sample size as of September 2019 based on the results of the only multicentre randomized controlled trial in which the percentage of gross total resection in the SSP and LP were 93% and 73%, respectively [14]. The sample size calculated by PASS version 15 is 58 participants per group (overall sample = 116 participants) according to the above data with a power of 80%, an alpha risk of 5%, and an estimated shedding rate of 8%.

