## Statistical methods

### Statistical methods for primary and secondary outcomes {20a}

All analyses will be performed using the SPSS software, version 25 (IBM Corp.) with a two-sided significance level of .05 unless otherwise stated. Continuous quantitative variables are expressed as numbers, means, standard deviations, and medians. Comparisons between proportions for the categorical variables will be performed using the chi-square test, Fisher’s exact test, or Mann-Whitney *U* test. In addition, Student’s *t* test and non-parametric analysis will be used for continuous variables with and without normal distributions. Differences in the percentage of gross total resection, facial nerve function, hearing function, general complications, and special complications between the SSP and LP groups will be evaluated using Fisher’s exact test or chi-squared test. Differences in the surgical positioning time, time of operation, hospital stay, and total hospitalization fee between the SSP and LP groups will be evaluated using Student’s *t* test or Mann-Whitney *U* test. Regression analysis will be used to evaluate the influence of SSP versus LP, tumour size, and surgeons on the percentage of gross total resection, as well as SSP versus LP, tumour size, surgeons, and the percentage of gross total resection on facial nerve function and hearing function. Association of the time of operation with SSP versus LP, tumour size, the percentage of gross total resection, and surgeons will be evaluated using ANOVA. If the patient has a PFO, he or she will not be excluded from the study but analysed according to the SSP group they were originally assigned after the LP surgery.

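### The stated 80% power makes no allowance for the planned switch of semi-sitting patients with a PFO to lateral surgery, although they are analysed as semi-sitting

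*Protocol article*

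**What the plan says.** **Sample size {14}.** The calculation rests on the primary endpoint and on one earlier randomised trial, in which "the percentage of gross total resection in the SSP and LP were 93% and 73%, respectively". PASS gives 58 per group, 116 in all, "according to the above data with a power of 80%, an alpha risk of 5%, and an estimated shedding rate of 8" per cent. The section does not mention PFO, a change of position or dilution of the effect.

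**Table 2.** Under the withdrawal criteria stands the entry "Patient has a patent foramen ovale". Footnote a describes transoesophageal echocardiography (TEE) as the screening method for patients planned for SSP. Footnote b says of a patient with a PFO that "he or she will not be excluded from the study, but the surgical position originally assigned will be changed to LP".

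**Statistical methods {20a}.** Such a patient is "analysed according to the SSP group they were originally assigned after the LP surgery". Tests are made "with a two-sided significance level of .05 unless otherwise stated", and the primary comparison is by Fisher's exact or chi-squared test.

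**The concern.** Three rules are set in one document and do not fit together: a sample size built on the full 20-point contrast, a rule that moves some SSP patients to LP surgery, and a rule that still counts them as SSP. Screening is described only for planned SSP, so switching runs one way, and every switch pulls the SSP rate towards the LP rate. The 8% shedding rate does not cover this, because switched patients are not lost: they stay in the denominator.

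At stake is the power of the primary comparison. If many patients switch, a non-significant result would say less about surgical position than a reader of the sample size section would suppose. The as-randomised difference would also be smaller than the effect in patients who can actually be operated on in SSP.

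**Working it through.** **Inputs from the protocol.** Rates 0.93 and 0.73, power 80%, alpha 5%, loss 8%, 58 per group (Sample size {14}); two-sided testing, Fisher's exact or chi-squared test (section 20a).

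**Inputs assumed.** f, the share of SSP-allocated patients switched to LP, is not in the documents and is shown as a range. Switched patients are taken to have the LP rate of 0.73. The cited 0.93 is taken not to include such switching already.

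**Step 1: reproduce 58 per group.**
- Pooled variance: n = [1.960 × √(2 × 0.83 × 0.17) + 0.842 × √(0.93 × 0.07 + 0.73 × 0.27)]² / 0.20² = 54.2, so 55. Then 55 / 0.92 = 59.8, so 60.
- Unpooled variance: n = (1.960 + 0.842)² × (0.0651 + 0.1971) / 0.04 = 51.4, so 52. Then 52 / 0.92 = 56.5, so 57.

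The stated 58 lies between the two. After 8% loss, 58 × 0.92 = 53.4, or about 53 evaluable per arm. Power there is 79.1% by the pooled formula and 81.1% by exact enumeration of the uncorrected chi-square test. The stated figure is therefore reproduced, with almost no reserve.

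**Step 2: dilute the SSP rate.** Under the as-randomised rule, SSP rate = 0.93 × (1 − f) + 0.73 × f = 0.93 − 0.20 × f.

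**Step 3: exact power of the uncorrected chi-square test against 0.73, two-sided 5%.**

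| f (assumed) | SSP rate | 53 per arm | 58 per arm |
|---|---|---|---|
| 0 | 0.930 | 81.1% | 85.1% |
| 1% | 0.928 | 80.1% | 84.2% |
| 2% | 0.926 | 79.0% | 83.2% |
| 5% | 0.920 | 75.5% | 80.0% |
| 10% | 0.910 | 69.5% | 74.2% |
| 20% | 0.890 | 56.9% | 61.6% |
| 25% | 0.880 | 50.6% | 55.0% |

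Power passes below 80% just above f = 1% with 53 per arm, and at about f = 5% with 58 per arm.

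**Step 4: the other permitted test.** Fisher's exact test with 53 per arm gives 73.6% at f = 0 and 60.7% at f = 10%. The baseline thus depends on a choice of test that the protocol leaves open.

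**Step 5: size of trial that would hold 80%.** By the pooled formula, with 8% loss: f = 10% needs 71 / 0.92 = 77.2, so 78 per arm; f = 25% needs 109 / 0.92 = 118.5, so 119 per arm.

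**The case against.** - **The loss depends on an unstated figure.** No PFO proportion appears, and the range runs from trivial (79% at f = 2%) to severe (51% at f = 25%). This stands. The size can only be given conditionally.
- **The 8% may not apply to the primary endpoint.** Resection is judged from the operation video and imaging (Table 3), and MRI is done before discharge (section 18b). Later loss to follow-up need not remove the endpoint, although withdrawal for non-schwannoma pathology could. This stands, and is why the break point is a range of about 1% to 5%.
- **The cited 93% may already include switching.** If the earlier trial had similar switches and reported as randomised, part of the dilution is built in. The protocol does not say so; the possibility has to be named as an assumption.
- **A reader might infer that 58 is miscalculated.** It is not: step 1 reproduces it. The fault lies in the undiluted contrast behind it.
- **A reader might infer that Table 2 leaves the handling of PFO undecided.** That goes too far. The entry carries footnote b, section 20a repeats the rule, and read together they keep the patient, operate in LP and analyse as SSP. What remains is a heading at odds with its own footnote. If the heading alone were followed, patients would leave one arm only; pooled-formula power against 53 LP patients would be 76.4% at f = 10% and 73.0% at 20%, and the arms would no longer be comparable.
- **Analysing as randomised is sound.** Agreed. That analysis is not the fault.

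**Conclusion.** The point holds in conditional form. The protocol plans a one-directional crossover, keeps it in the primary comparison and allows nothing for it in the sample size. The stated 80% therefore applies only if essentially no SSP patient is switched.

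Under the assumptions listed above, the chi-square test drops below 80% once f exceeds about 1% (full 8% loss) or about 5% (no loss). At f = 10% power is about 70% to 74%, and at 25% about 51% to 55%. Fisher's test gives less throughout.

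The documents do not support the stronger statement that the trial's power is known to be some particular low figure: that would need f, the resection rate in switched patients and the make-up of the cited 93%, none of which they give.

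**What to change.** 1. In Sample size {14}, state that 80% assumes no PFO switching. Restate power for the as-randomised analysis from SSP rate = 93% − 20 points × f. Take f from the TEE results of the SSP arm, which needs no outcome data. Name the assumed rate in switched patients, the assumption about the cited 93%, and the test used.
2. Keep the as-randomised analysis as primary.
3. Reconcile the PFO entry under the withdrawal criteria in Table 2 with footnote b and section 20a.
4. Optionally, add a supportive complier-average estimate, the risk difference divided by (1 − f), using randomisation as the instrument and a bootstrap interval. It describes the effect in patients who can receive SSP; it does not restore power.

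The cost is protocol wording, a less favourable stated power and at most one extra analysis, with no added patients or procedures. Restating the figure makes it honest but does not bring power back to 80%; that would take the larger numbers in step 5.
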